#### Regular weighing and weight gain charts

All study community midwives will be issued with calibrated light weight portable weighing scales and instructed to use these for this study. Women will be weighed by their midwife at each antenatal appointment. After 12 weeks of pregnancy in usual antenatal care there are up to eight consultations or opportunities for the intervention to take place. The explicit behavioural goal of the intervention will be for women’s weight gain to follow the trajectory of the midpoint line of the healthy weight gain zone of their IOM chart (Fig. 2a–c) to prevent excessive weight gain. In line with NICE guidance the goal will always be for weight gain, and never weight loss. The weight gain charts are personalised according to women’s weight and BMI category (healthy weight, overweight, obese) at recruitment.

Many women do not know their pre pregnancy weight therefore when the weight gain chart is prepared and customised at recruitment it will be assumed that women have gained average weight at recruitment in line with weeks of gestation according to their BMI category. BMI and therefore the BMI category weight chart used will be based on participants’ BMI when measured at recruitment.

#### Setting the parameters for gestational weight gain

The intervention will support women to stay on course for healthy overall weight gain by setting a maximum weight gain limit for each subsequent antenatal appointment that encourages women to stay within the two threshold lines on their weight chart. As used in the feasibility trial we will teach midwives a simple method for adjusting women’s maximum weight gain limit that aims to move women’s weight gain back to the healthy zone, but safely and slowly (see Fig. 2a–c). Women whose weight gain is within the appropriate range on the chart will be told they are gaining the ideal amount of weight and encouraged to maintain a healthy lifestyle. Women gaining too much weight will be encouraged to eat a healthy diet and restrict their intake of high fat and sugary foods and drinks and to participate in regular physical activity (walking). Women who are gaining too little weight will be referred by their midwife to the appropriate health professional in line with local practice. As we do not want women to lose weight at any stage in their pregnancy it may not be possible to meet the final target if early weight gain is excessive.

#### Advice about gestational weight gain and lifestyle

As part of the feedback from the weight gain charts, midwives will give messages about the importance of preventing excessive weight gain during pregnancy, address misconceptions about nutritional needs during pregnancy (e.g. “*eating for two*”, “*weight gain does not matter when you are pregnan*t*”*, “*you shouldn’t exercise when you are pregnant*”) and offer usual advice about healthy eating and exercise in pregnancy. This is intended as a brief intervention that could be implemented into routine care, so midwives will not be expected to engage women in detailed lifestyle counselling about how changes to diet and physical activity might be implemented; the focus will be on giving brief feedback and advice. Women will be encouraged to accumulate 30 min of moderate intensity physical activity (walking) each day in line with current recommendations [51, 52]. Brief advice about healthy eating will include portion control, decreasing energy dense foods, limiting sugar-sweetened beverages, increasing and/or maintaining consumption of fruit and vegetables. If women are already following a healthy lifestyle midwives will encourage continuation of these health behaviours and emphasise why it is important to do so during pregnancy. The focus of the intervention is on setting targets, providing feedback, and encouraging self-monitoring. It is not on detailed nutritional and exercise counselling.

#### Self weighing and monitoring of weight

Women will be asked to monitor weight by weighing themselves weekly and will be reminded to do so by their community midwife at each appointment. They will assess their progress towards the maximum weight gain limit set by their midwife on the weight gain chart; this will provide women with a visual picture of their weight gain progress to date and a prompt to take action if they are not on target. In addition women will be asked to write down their weight on their weight record card and set themselves a reminder to do so between appointments with the midwife (Fig. 3). Collectively these tasks are important for several reasons. We learnt from our feasibility trial that we needed to place greater emphasis on women self managing their weight between appointments and have established strategies to help achieve this. There are gaps of several weeks between some antenatal appointments (e.g. between 16–24 weeks of pregnancy) so it is important for women to be aware of their weight gain during these intervals, so that lapses can be identified early and correction implemented. The intervention seeks to encourage women to work in partnership with their midwife rather than relying entirely on the midwife for feedback before taking action. We also want women to become familiar and comfortable with using their weight gain chart to understand what their weight should be for each week of pregnancy.

Women who do not have scales at home will be given some to use at recruitment. At baseline women will be advised to check their weight when they get home on their own scales to assess whether their home scales are measuring the same weight as recorded by their midwife. Women who have scales that do not record weight accurately (within 0. 5 kg of the measured weight at recruitment) will be asked to contact the study coordinating centre which will issue new scales. Women will be encouraged to only weigh themselves once per week. Women will be encouraged to work out when and where they plan to weigh themselves and write down their weight on the record card. Helping women form implementation intentions should increase adherence.

#### Intervention leaflet

Women randomised to the intervention will be given a brief leaflet outlining the key principles as described here and it will explain to women why it is important to weigh themselves each week and check their weekly maximum weight gain limit. Examples of how women might implement weekly weighing (implementation intentions) will also be included in the leaflet.

#### Training community midwives to deliver the intervention

The training module was developed for the feasibility trial and modified based on feedback from community midwives. It takes 60 min to deliver and is designed for group training, with information on study eligibility criteria, recruitment procedures and the importance of adhering to protocol. It describes the intervention, including information on the consequences of weight gain during pregnancy, instructions about how to weigh and plot weight on the chart, how to give feedback on the weight gain chart and example messages, set weight gain limits using the charts, and examples of educational and motivational messages about gestational weight gain, diet and physical activity during pregnancy. Midwives will practice completing the weight gain charts using prepared case studies. The training module will include example cases demonstrating how the intervention works in practice, the kind of questions likely to be raised by women and ideas of how to deal with them.

### Intervention implementation and fidelity

Early in the study we will select a random sample of 50 charts from different midwives across study sites to be checked by the research team for completion and accuracy when women are 20 weeks pregnant. This will provide an indication if additional training of midwives is required. To provide a measure of intervention implementation in the intervention group as a summary on trial completion we will obtain participants’ weight gain charts and weight record cards and assess accuracy. From the weight gain chart we will check whether weight had been measured, plotted and recorded by community midwives and if maximum weight gain limits were calculated and recorded correctly at each antenatal appointment. We will assess how frequently midwives set maximum weight targets and how often they encouraged women to weigh themselves weekly. We will assess how often women in the intervention group completed their weekly weight record to measure their engagement with the intervention. We will assess whether midwives delivered advice according to the protocol in the intervention group and did not contaminate the trial in the usual care group by asking women in a questionnaire about the advice given by their community midwife about weight control, eating, and physical activity.

### Usual care

The usual care group will receive standard maternity care according to local health care provision and no other intervention. NICE [42, 53] state that women should be given information on diet and exercise early in pregnancy. NICE [42, 53] do not currently recommend that midwives routinely weigh women or give information about optimal weight gain during pregnancy. This is not a trial about giving lifestyle advice so midwives will not be asked to refrain from offering usual advice about diet and exercise early in pregnancy. This trial is testing the addition to usual care of an intervention where midwives set targets for healthy weight gain, weigh women and encourage women to monitor their weight to ensure they stay on target, and give feedback on every visit for antenatal care.

### Descriptive data

Data will be collected about participants’ demographic details, smoking status and weight management history at recruitment.

### Data, outcomes and process measures

See Table 1 for a comprehensive list of the outcomes and process measures in the study.

**Table 1 Tab1:** Data, outcomes and process measures

Recruitment measures		
Eligible participants not consented		
Number declined at booking scan		
Number of participants randomised		
	Usual care group	Intervention group
Process measures		X
Accuracy and completion rates of weight chart by midwives		X
How frequently did midwives encourage women to weight themselves weekly		X
Frequency of regular weighing by participants as recorded on weight record cards		X
Outcomes		
Weight	X	X
Depression and anxiety (HADS) [55]	X	X
Physical activity (Physical activity in pregnancy questionnaire [56]	X	X
Diet quality (Southampton food frequency questionnaire) [57]	X	X
Questions about diet and physical activity advice midwives have given during pregnancy	X	X
Maternal and neonatal complications (obtained from electronic hospital records)	X	X

### Baseline assessment

All trial women will be weighed by the research team using calibrated scales and have their height measured with excess clothing (i.e. shoes and coats) removed. The study baseline questionnaires will also be completed measuring anxiety and depression, physical activity and diet quality.

### Follow up

We rehearsed several strategies in our feasibility trial for ensuring high follow up rates for our primary outcome in this trial (>90 % obtained in our feasibility trial). Pregnant women are routinely seen by their midwife at 38 weeks of pregnancy and they will be weighed at this appointment for the purpose of this study. At recruitment all women will have a sticker inserted into their hand held pregnancy notes on the page where midwives normally record routine medical information; weight and weeks of pregnancy will be recorded on this sticker. Women who do not attend their 38 week appointment will be contacted and alternative arrangements for them to be weighed will be made. We have chosen 38 weeks of pregnancy as the primary outcome because this time represents nearly the end of pregnancy and only 7–10 % of women deliver before this gestation [54], which leads to a low rate of unavoidable loss to follow-up. As women will see their community midwife weekly until the end of pregnancy after 38 weeks, this provides several more opportunities to catch up with women after 38 weeks if women miss the 38 week appointment or the midwife does not weigh women. As a consequence, we believe loss to follow up will be low. At 38 weeks, the study team will post a questionnaire to women to assess depression and anxiety, physical activity and diet quality. The team will send one postal reminder to non responders.

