**Fig. 2 Fig2:**
[figure not shown]
**a**: Example of how to set weight gain limits for antenatal appointments. The woman is recruited at 12 weeks gestation and her weight is plotted on the chart for this week of pregnancy. The woman is advised that her weight should follow the dotted line drawn through the ideal weight gain zone on the chart (unshaded area). The woman is due to be seen again by her midwife at 16 weeks gestation therefore the midwife draws a vertical line at 16 weeks gestation to meet the dashed line in the unshaded ideal weight gain zone to ascertain what the maximum weight target should be for 16 weeks gestation. In this example the woman is advised by her midwife that ideally her weight should be no more than 63.5 kg at 16 weeks gestation. The midwife repeats the procedure at each antenatal appointment. **b**: Example of how to set weight gain limits for antenatal appointments. At 16 weeks of pregnancy the midwife weighed the woman and plotted her weight on the chart. In this example the woman weighed 63.5 is 16 weeks gestation which was the maximum weight limit set at her previous appointment at 12 weeks gestation. The midwife then set the maximum weight target for the next antenatal appointments which was scheduled for 25 weeks gestation. The midwife draws a vertical line at 25 weeks of gestation to meet the dashed line in the unshaded ideal weight gain zone to ascertain what the maximum weight target should be for 25 weeks gestation. In this example the woman should ideally weigh no more than 67 kg at 16 weeks gestation. **c**: How to set and adjust maximum weight targets if women gain too much weight. At 25 weeks gestation the midwife weighed the woman and plotted her weight, which was 70 kg. This was above the maximum weight target set at the previous appointment at 16 weeks gestation. The midwife therefore redraws the ideal weight trajectory line starting from the plotted weight at 25 weeks gestation to the central point in the unshaded weight zone until 42 weeks gestation. The midwife uses this new line to set the maximum weight target for the next antenatal appointment scheduled for 28 weeks gestation. The midwife draws a vertical line at 28 weeks of gestation to meet the dashed line in the unshaded ideal weight gain zone to ascertain what the maximum weight target should be for 28 weeks gestation. The midwife advised the woman that her maximum weight target for 28 weeks of pregnancy was 70.6 kg

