### Outcome measures

The primary outcome is the proportion of participants per group who exceed the IOM guidelines for gestational weight gain according to their early pregnancy BMI category from baseline to 38 weeks of pregnancy. Secondary outcomes are the difference in weight gain per weeks of pregnancy between the groups**,** difference in total weight from baseline to 38 weeks of pregnancy between the groups and difference in changes in psychological health, physical activity and diet quality between the groups from baseline to 38 weeks of pregnancy.

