### Post study data collection

The weight gain charts will be retrieved from the pregnancy notes after women have had their baby. We do not expect to have sufficient power within this trial to detect statistically significant differences in maternal and neonatal complications but these data will be obtained from medical records at each hospital and described in the trial reports to contribute to future meta analyses. The following information on pregnancy will be collected mode of delivery, inpatient days for the mother, maternal ICU admission, preeclampsia, pregnancy induced hypertension, gestational diabetes, maternal sepsis, preterm delivery, miscarriage, stillbirth, shoulder dystocia, treatment for jaundice, admission to the neonatal intensive care unit (duration of stay if relevant and inpatient days), neonatal death and 1 and 5 min Apgar score and neonatal sepsis. Data on infant birth weight and gestational age at delivery will also be collected from hospital electronic records.

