### Statistical analysis

Baseline characteristics including age, social class, ethnicity and parity will be presented by randomisation group using summary statistics. The primary analysis will focus on the proportion of women who exceed the IOM guidelines for gestational weight gain at ~38 weeks of pregnancy (primary outcome). The difference in these proportions between the groups (and odds ratio) will be calculated along with associated confidence interval using mixed effects logistic regression modelling. The analysis will adjust for BMI category (healthy weight, overweight, obese) and site (Birmingham, Dudley, Oxford, Warwick) as fixed effects and midwife as a random effect. Missing weight data for births occurring after 37 weeks (excluding pregnancy loss), will be imputed using multiple imputation. Linear mixed modelling will be used to compare the secondary outcomes of weight gain per weeks of pregnancy, depression, anxiety, physical activity and diet recorded at ~38 weeks of pregnancy. Mother and baby pregnancy complication rates will be summarised by group. In a planned but exploratory subgroup analysis, BMI categories (healthy weight, overweight, obese) will be compared for the primary outcome by its inclusion as an interaction term (intervention by BMI category) in the modelling. There are no other planned subgroup analyses. A sensitivity analysis of the primary outcome will be performed without imputing missing weights. Treatment effects, 95 % confidence intervals, and two-sided p values will be reported for all comparisons. Analyses will be undertaken using an intention to treat approach. Full details of analysis will be pre-specified in a separate statistical analysis plan.

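### The mood, activity and diet questionnaire is posted only at 38 weeks, the time point it is meant to measure, so a non-trivial share of returns is likely to be completed after birth

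*Protocol article*

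**What the plan says.** All places are in the Protocol article.

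- **Outcome measures** sets the time point for these secondary outcomes: "difference in changes in psychological health, physical activity and diet quality between the groups from baseline to 38 weeks of pregnancy".
- **Statistical analysis** compares "depression, anxiety, physical activity and diet recorded at ~38 weeks of pregnancy" by linear mixed modelling.
- **Follow up** fixes the mailing: "At 38 weeks, the study team will post a questionnaire to women to assess depression and anxiety, physical activity and diet quality". It then adds: "The team will send one postal reminder to non responders". No reminder interval is given.
- **Follow up** also justifies 38 weeks on the ground that "only 7–10 % of women deliver before this gestation", and notes that later weekly visits allow a missed measurement to be caught up. Both arguments are made for weight, not for the questionnaire.
- **Post study data collection**: "Data on infant birth weight and gestational age at delivery will also be collected from hospital electronic records".

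The article does not say whether women who deliver before 38 weeks are sent a questionnaire.

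**The concern.** A posted form has to arrive, be completed and be sent back, and a reminder comes later still. If posting starts at 38 weeks, every completion is later than 38 weeks. A return a few days later from a woman who is still pregnant fits the analysis section's approximate wording. A return after birth does not, because mood, activity and diet in the first days with a newborn are a different quantity from the same measures in late pregnancy. Table 1 names a pregnancy-specific activity questionnaire, which fits poorly after delivery.

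The anxiety score carries most of the weight. The Background section on target setting and regular weighing reports the worry that weighing and feedback may cause anxiety. The anxiety and depression scale in Table 1 is the only between-group measure of this that the article names. Adverse events are not all monitored by group, and no data monitoring committee is planned. If postnatal scores are mixed in, a real difference is harder to see. If they are removed, data are lost, mainly from women who deliver earlier or reply late.

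**Working it through.** The plan gives no figure for return time or for the share completed after birth, so there is nothing of its own to reproduce. The check asks how large that share could be.

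**Inputs from the article**
- Share delivered before 38 weeks, p = 0.07 to 0.10 (Follow up). So 90–93% of births are still to come at posting.
- The weight chart runs to 42 weeks (Fig. 2 caption: "to the central point in the unshaded weight zone until 42 weeks gestation"). It is used here only as a convenient end of the delivery span.

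**Assumptions (not in the article)**
- Return lags of 3, 7, 14 and 21 days.
- Three models for the timing of birth:
  - A: normal, SD assumed 1.4–1.8 weeks, mean solved from p.
  - B: normal, mean assumed 39.3–40.0 weeks, SD solved from p.
  - C: births spread evenly over weeks 38 to 42.

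The single percentage in the article cannot fix both a mean and an SD, so one of the two is assumed in A and in B.

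**Formula.** With F(t) the share of all women delivered by week t, the share of women undelivered at posting who have given birth by week t is

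(F(t) − p) / (1 − p).

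This leaves out births before posting.

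**Worked examples at one week (t = 39)**
- A, p = 0.07, SD 1.8: mean = 38 + 1.476 × 1.8 = 40.66; F(39) = 0.179; (0.179 − 0.07)/0.93 = 0.117.
- A, p = 0.10, SD 1.4: mean = 38 + 1.282 × 1.4 = 39.79; F(39) = 0.285; (0.285 − 0.10)/0.90 = 0.206.
- B, p = 0.10, mean 39.6: SD = 1.6/1.282 = 1.25; F(39) = 0.315; (0.315 − 0.10)/0.90 = 0.239.
- C: 7/28 = 0.25.

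**Share of women undelivered at 38 weeks who have given birth, by lag**

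| Lag | A | B | C | All |
|---|---|---|---|---|
| 3 days | 4–7% | 6–11% | 11% | 4–11% |
| 7 days | 12–21% | 17–32% | 25% | 12–32% |
| 14 days | 31–51% | 44–77% | 50% | 31–77% |
| 21 days | 54–78% | 71–97% | 75% | 54–97% |

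The low end of A comes from SD 1.8, which places 17–23% of births after 42 weeks, so it is a cautious lower limit.

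**Mixed reply patterns** (weighted averages of the rows, reply time taken as unrelated to birth)
- 90% reply at 3 days, 10% at 14 days: from 0.9 × 0.041 + 0.1 × 0.309 = 7% (A) up to 17% (B).
- 70% reply at 7 days, 30% at 21 days: from 0.7 × 0.117 + 0.3 × 0.544 = 25% (A) up to 52% (B).

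**Effect on a difference.** If a share q of returns is postnatal and, as an unfavourable assumption, the arms do not differ after birth, the expected difference shrinks to (1 − q) of its size. That is 83–93% for the fast pattern and 48–75% for the slow one. If the difference persists after birth, only noise is added.

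**Earlier posting.** For a form posted at 36 weeks and completed within two weeks, the share completed after birth is (F(38) − F(36))/(1 − F(36)), which cannot exceed F(38) = 7–10%. This bound uses only the article's own figure. The matching figure for posting at 38 weeks is 31–77%.

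**The case against.** The strongest reply is that the size is unknown and the handling belongs elsewhere. The article gives no reply times. If nearly all women answered within three days, only 4–11% of forms would be postnatal. A return window, a rule for post-birth forms and the recall period of each instrument may stand in the full protocol or the analysis plan, neither of which is shown. Nothing in the article says that postnatal forms count as 38-week values. Posting at 36 weeks would also move these measures away from the declared time point and from the 38-week weight.

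Much of this stands. The absence of handling rules from a condensed article is no fault. What remains is the mailing date, which the article does fix. An analysis window can discard a late return but cannot recover an antenatal score that was never collected.

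Three stronger readings are tempting, and the document does not support them:

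- A reader might infer that a sizeable share *will* be postnatal and that the stated outcome will not be measured. This depends on reply times, instrument wording and handling rules that are not given.
- A reader might take the 18–29% of all women delivered by 39 weeks under model A as the share of one-week returns. That figure includes births before posting, and the article does not say those women are sent a form. Among women undelivered at posting, the same model gives 12–21%.
- A reader might infer bias between arms because the intervention group is prompted at each appointment. Those prompts, in the section on self weighing, concern weekly weighing and not return of the questionnaire. Posting and reminder are described without any difference by group.

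**Conclusion.** The mailing schedule does not fit the stated time point. Completion must fall after 38 weeks, while most births are still to come, so completion after birth is likely for a non-trivial share. The size rests on assumed reply times and birth models: single figures to about a tenth at three days, roughly an eighth to a third at one week, and a third to three quarters at two weeks, when reminder replies could plausibly begin. The direction is the same in every model tried.

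The consequence is noise, possible dilution or lost data for the questionnaire-based secondary outcomes, anxiety included. Bias between arms would need reply speed or gestation at delivery to differ by group, which is possible but not shown. The primary outcome, weight recorded by midwives, is untouched. This is a cheap improvement worth making and does not threaten the main result.

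**What to change.** 1. Send the questionnaire and its reminder earlier, for example posted at about 36 weeks with the reminder at about 37 weeks, or hand it out at an antenatal visit by 38 weeks. Most forms would then be completed in pregnancy, at or just before 38 weeks.
2. Add a completion date to the form. With the gestational age at delivery that is already collected, it identifies post-birth returns.
3. Use these dates for a sensitivity analysis that separates returns made before and after birth. The detailed rules for late returns can be left to the analysis plan.

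The cost is a changed mailing date and one extra field. The small downside is that some values would be measured one to two weeks before the 38-week weight, so the outcome definition should be worded to match.
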